#### Functional Magnetic Resonance Imaging Data Analysis

On the MATLAB R2013b (Mathworks, Natick, MA, United States) platform, the statistical parametric graph software (SPM12.0^1^) and data processing assistant for rs-fMRI software (DPARSF^2^) will be used for data processing and analysis. DPARSF is a SPM-based rs-fMRI data processing software (Yan et al., 2016). Preprocessing steps include (Lv et al., 2018; Ll et al., 2020): (a) removing the first 10–20 time points and slice timing, (b) head movement correction (head movement exceeding 2 mm in any direction or head rotation exceeding 2° will be ruled out), (c) normalization (in accordance with the Montreal Neurological Institute EPI template, each voxel is resampled to 3 mm × 3 mm × 3 mm), (d) delinear drift, (e) removal covariate (confounding effects of head movement parameters, white matter, and cerebrospinal fluid signals), (f) filter (0.01–0.1 Hz), and (g) smooth (8 mm full-width half-maximum Gaussian). Then, the ReHo, fALFF, and FC values will be calculated. The ReHo analysis is a voxel-based measurement that calculates the Kendall coefficient of concordance between a voxel and its surrounding 26 voxels, which is the ReHo value of that voxel (Zang et al., 2004). The ReHo analysis determines the synchrony of adjacent regions, and high values indicate high consistency of regional brain activity. The ALFF measurement is the root mean square of the power spectrum of the BOLD signal in the range of 0.01–0.1 Hz for each voxel. Afterward, the ALFF value of each voxel divided by the full-band ALFF sum is the fALFF value, which can reflect the strength of brain self-activity (Toole et al., 2005). FC was examined by using a seed voxel correlation approach. The cerebellar vermis will be selected as the seed region based on the stimulation target. In SPM12, after bandpass filtering and linear-trend removal, a reference time series for the seed will be extracted by averaging the fMRI time series of voxels. Then, correlations will be computed between the seed reference and the rest of the brain in a voxelwise manner. Finally, an individual relativity value (*r*-value) map will be created, and the correlation coefficients in each voxel will be transformed to *z* values by using Fisher’s *r*-to-*z* transformation to improve normality before performing random effect *t*-tests. The AlphaSim will be used for correction to obtain the adjustment statistical threshold value of *P* < 0.05. Data will be analyzed by the independent-samples (between-group comparison) or paired (within-group comparison) *t*-test.

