A randomized controlled clinical trial will be conducted to investigate the rehabilitation effect of the cerebellar vermis intervened by iTBS in stroke patients with balance dysfunctions. Furthermore, the resting-state functional magnetic resonance imaging (rs-fMRI) will be used to analyze the functional connections between cerebellar vermis and other areas of the cerebral cortex, and clarify the neural remodeling mechanism. We propose a hypothesis that iTBS of cerebellar vermis can promote the recovery of balance function after stroke. This study may provide new insights into the therapeutic efficacy and underlying neuroplasticity mechanisms of cerebellar vermis intervention.

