### Sample Size

The sample size was calculated using a G*power of 3.1.4. The effect size was calculated as 0.28 based on the BBS from a study reported by Koch et al. (2018). To achieve 95% power with an alpha error of 5%, a sample size of 30 patients will be required. Allowing for a dropout rate of 20%, at least 38 patients are necessary. To ensure enough power to detect this typical difference, we will aim to recruit 40 patients (20 patients per group).

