#### Secondary Outcomes

In addition to the BBS scores, FMA-LE, MBI, and rs-fMRI will be measured with the following tests.

Fugl–Meyer assessment of the lower extremity has been widely used in the assessment of the motor function of patients with stroke and has good prediction, reliability, and sensitivity to interventions (Balasubramanian et al., 2016). In addition, the reliability of the FMA scale is >75% between different raters and >88% within the same rater (Hernández et al., 2021). The FMA-LE consists of 17 items, with each item scoring a minimum of 0 and a maximum of 2 points, resulting in a maximum total score of 34 points. A high score results in good motor function of the lower extremity.

The MBI, one of the main scales used to measure the patients’ abilities to perform activities of daily living, has a reliability of 88% in patients with ischemic stroke (Yang et al., 2021). The MBI consists of 10 items, with a full score of 100 points. A high score results in good independence of the patient’s life.

All subjects will undergo rs-fMRI scans. Regional homogeneity (ReHo), fractional amplitude of low-frequency fluctuation (fALFF), and functional connectivity (FC) will be calculated to measure the local and global FC networks related to motion function. All images will be acquired by professional personnel in a 3.0T, 8-channel MRI scanner (Siemens Skyra, Germany). During scanning, subjects will be required to keep awake, breathe quietly, lie flat on the bed, fix their heads to minimize the movement of their heads and other parts, and try not to do any active thinking activity. It will take approximately 40 min to complete the test. Conventional T1 structural image parameters are as follows: repetition time (TR) = 2,000 ms, echo time (TE) = 20 ms, field of view (FOV) = 240 mm × 240 mm, slice thickness = 4 mm, slice spacing = 4 mm, flip angle (FA) = 90°, and 36 slices. Functional images will be acquired using T1-weighted gradient echo planar imaging (EPI) sequence in the axial plane with the following parameters: TR = 2,000 ms, TE = 30 ms, FOV = 240 mm × 240 mm, slice thickness = 4 mm, FA = 90°, and 35 slices.

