## Discussion

This 3-week randomized controlled clinical trial aims to study whether cerebellar vermis iTBS can improve balance function in patients with stroke. In this perspective of experiment design, our study puts forward some methodological concerns that should be discussed, including the large variation in balance function among enrolled patients. Therefore, a stratification approach will be adopted in this study to divide all participants into two subgroups in accordance with the BBS. In addition, we set a sham stimulation group to eliminate the placebo effect of iTBS intervention. After careful consideration of all factors, including the feasibility of the study and the treatment time pattern of the hospital where the experiment will be conducted, we set sessions from Monday to Friday for 3 weeks. Also, outcome will be evaluated at pre-intervention, the end of first, second, and third week of post-intervention. We want to compare the efficacy at different time points, and to explore the earliest time when the treatment can take effect. Our study will use rs-fMRI rather than task state fMRI for measuring the iTBS-induced effects, although task state fMRI can reflect the fMRI images of the brain when performing specific tasks. What we considering is that our subjects are post-stroke patients with motor dysfunction, there may be great differences in the quality of tasks completed by stroke patients, which may affect the results.

In this study, we expect that the cerebellar vermis iTBS can promote the recovery of balance function after stroke. This hypothesis is based on the following evidence.

Maintaining balance depends upon a complex coordination and integration of multiple systems in the body, including the visual system, vestibular system, and auditory system. As pointed out in fMRI research, the cerebellar vermis and the visual network have a strong functional connection (Kellermann et al., 2012; Li et al., 2012). Recent evidence displayed that the vermis coordinates eye and body movements, and provides visual and auditory input related to balance (Fujita et al., 2020). In addition, studies have shown that the vermis participates in regulating vestibular system and maintaining head position (Lam et al., 2016). Balance is best maintained when all inputs are integrated together. Therefore, the cerebellar vermis plays an essential role in the active maintenance of body balance.

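### Head motion is controlled only within each scan; the group imaging tests have no between-arm motion check and no motion sensitivity analysis, so residual motion could be read in part as remodeling.

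*Protocol article*

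**What the plan says.** All references are to the protocol article.

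- **Functional Magnetic Resonance Imaging Data Analysis, step (b):** after realignment, "head movement exceeding 2 mm in any direction or head rotation exceeding 2° will be ruled out". Motion up to those limits is kept.
- **Same section, step (e):** nuisance regression removes "confounding effects of head movement parameters, white matter, and cerebrospinal fluid signals" within each subject, before the metrics are calculated. The number and form of the movement parameters are not given.
- **Same section, group tests:** "Data will be analyzed by the independent-samples (between-group comparison) or paired (within-group comparison" is how the text describes the group step, and the test named is the t-test. No covariate appears, and no comparison of motion between arms or visits is described.
- **Secondary Outcomes:** during scanning, subjects are to "fix their heads to minimize the movement of their heads and other parts". This applies to both arms.
- **Introduction:** rs-fMRI is included to "clarify the neural remodeling mechanism". Table 1 lists the three rs-fMRI measures among the key secondary outcomes.
- **Discussion:** the article cites evidence that "the vermis participates in regulating vestibular system and maintaining head position".

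**The concern.** Each motion safeguard acts on one scan at a time. None asks whether the remaining motion differs between real and sham stimulation, or between the first and second scan. If the movement regressors are head-position parameters, linear regression removes the part of the artefact that is linear in position. Artefact that follows the size of a displacement can remain. The exclusion limit of 2 mm is two thirds of the 3 mm resampled voxel, so appreciable motion is admitted.

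At baseline, randomisation balances motion on average. At the second scan motion is a post-treatment measurement, and randomisation no longer guarantees balance. The paired tests are weaker still: both arms receive three weeks of balance-focused rehabilitation, and any change in how still patients lie enters the before-after contrast directly.

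At stake is the mechanistic conclusion. The rs-fMRI measures are the trial's evidence for remodeling, and the planned tests cannot separate a neural change from a change in residual motion.

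**Working it through.** **1. The plan's own figure, for the sample size per arm.** The article states "The effect size was calculated as 0.28 based on the BBS" and "To achieve 95% power with an alpha error of 5%, a sample size of 30 patients will be required". I take 0.28 as Cohen's f in a repeated-measures group-by-time test with 2 groups and 4 time points, and assume correlation 0.5 and sphericity 1.

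- Noncentrality = f² × N × m / (1 − ρ) = 0.0784 × 30 × 4 / 0.5 = 18.8.
- Power is 0.959 at N = 30 and 0.944 at N = 28, so 30 reproduces.
- 30 / (1 − 0.20) = 37.5, rounded up to 38, which also reproduces.

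The target is 20 per arm. For imaging I assume 18 usable per arm (36 in all), and show 15 and 20 as bounds.

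**2. Effect of an unmodelled motion difference.** The documents give no motion data, so these inputs are assumptions:

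- r = correlation across patients between change in motion and change in the map value: 0.2 to 0.4.
- d = arm difference in motion change, in SD units: 0.3 to 0.8.

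The spurious arm effect is r × d. The noncentrality of the two-sample t-test is r × d × √(n/2). With n = 18, √(18/2) = 3 and df = 34.

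| r | d | spurious effect (SD) | noncentrality | error rate of a 5% test |
|---|---|---|---|---|
| 0.2 | 0.3 | 0.06 | 0.18 | 5.4% |
| 0.3 | 0.5 | 0.15 | 0.45 | 7.2% |
| 0.4 | 0.8 | 0.32 | 0.96 | 15.4% |

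If r is allowed to fall to 0.1, the range is 5.1% to 13.5% at 15 per arm and 5.1% to 16.7% at 20 per arm. If r = 0 or d = 0, the rate stays at 5%.

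**3. A check closer to the planned pipeline.** A small time-series simulation used 220 volumes, regression of motion parameters with white-matter and CSF signals, a 0.01–0.1 Hz filter, artefact proportional to displacement, and motion 30% lower in one arm (120 trials per setting). The correlation between FC change and motion change was 0.05 to 0.22, and the absolute bias 0.02 to 0.11 SD. In the formula above:

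- 0.02 × 3 = 0.06, error rate 5.04%.
- 0.11 × 3 = 0.33, error rate 6.2%.

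This lies at and below the bottom of the assumed range in step 2.

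**4. Does the covariate gain precision?** The variance removed is r². At the simulated correlations this is 0.05² = 0.25% to 0.22² = 4.8%. Estimating the covariate costs about 3% at N = 36. The net result runs from a slight loss to a negligible gain, so precision is no argument for it here.

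All these rates describe one prespecified test. The planned maps are voxelwise with an AlphaSim correction, for which the documents allow no equivalent figure.

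**The case against.** **The article is condensed, and second-level covariates may stand in a fuller plan.** This has weight and keeps the point small. But the section is not silent: it runs from preprocessing through the multiplicity correction to a named group test, and a t-test has no place for a covariate. The point concerns that stated choice.

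**Motion is already controlled.** A reader might infer from the group tests that motion is uncontrolled. The documents do not support that: they set an exclusion limit, a nuisance regression and head fixation in both arms. The regression may also be richer than plain position parameters, since its form is not stated. Only residual motion is in question.

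**The vermis link is thin.** A reader might also infer that iTBS will make the real arm lie stiller, because the Discussion ties the vermis to head position. That sentence belongs to an argument about body balance. It says nothing about millimetre movements of a supine, fixed head, and patients with cerebellar or brainstem stroke are excluded. Both arms receive the same kind of rehabilitation, so motion may change in both. A motion difference between arms is possible, not shown.

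**Adjustment is not neutral.** If treatment affects motion at the second scan, conditioning on it no longer estimates the randomised effect, and shared causes of motion and brain measures could bias the result in either direction. This stands, and it rules out making the adjusted model decisive.

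**Conclusion.** The point holds as a modest gap in a secondary, mechanistic analysis. No motion comparison between arms or visits is stated, and the group tests carry no motion term. Residual motion at the second scan could therefore contribute to a difference attributed to remodeling, most directly in the paired tests.

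The size is unknown. An error rate near 15% needs both assumed inputs at their upper ends (r = 0.4 and an arm difference of 0.8 SD); the simulation supports about 5% to 6%. Both depend on motion differing between arms, for which the documents give no evidence. A stronger conclusion, that the imaging contrasts are invalid or that an expected treatment effect on stillness will bias them, does not follow from the text. The primary BBS analysis is not affected.

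**What to change.** In the imaging analysis section:

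1. Compute mean framewise displacement for each scan from the realignment parameters already estimated in step (b), and report it by arm and scan.
2. Prespecify a sensitivity version of the group models for ReHo, fALFF and FC with centred mean framewise displacement as a covariate (its change, where change maps are analysed). Show it beside the planned t-tests.
3. State that if motion differs between arms, or a result does not persist after adjustment, the remodeling interpretation may reflect motion. Do not make the adjusted model the sole decision rule.

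The cost is analysis wording, one value per scan from existing output, and one degree of freedom of about 34. Recruitment, scanning and treatment do not change. The drawback is that the adjusted estimate conditions on a variable that treatment may affect and is not the pure randomised effect, which is why it belongs in a sensitivity analysis. It should be fixed before the maps are seen.

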Key inclusion and exclusion criteria	Inclusion criteria: (a) have a diagnosis of stroke confirmed by CT and/or MRI, (b) have their first-ever unilateral ischemic stroke between 1 and 6 months of onset, (c) are 40–75 years old, (d) presented with a balance dysfunction with a Berg score between 0 and 40, (e) can follow simple verbal commands or instructions, and (f) can cooperate in signing informed consent forms. Exclusion criteria: (a) with contraindications involving TMS and fMRI (e.g., intracranial implant, cardiac pacemaker, implanted drug pumps, and pregnancy), (b) with cerebellum or brainstem stroke, (c) with balance dysfunction before stroke, (d) with serious diseases that may contribute to condition progression, (e) with severe deficits in communication or executing commands that prevent cooperation with assessment and treatment, (f) who are taking psychotropic drugs, and (g) who are currently enrolled in other clinical trials.
Study type	Interventional Allocation: randomized intervention model Masking: participants and assessors-blinded Assignment: parallel Primary purpose: treatment
Date of first enrolment	Not yet started
Target sample size	40
Recruitment status	Recruiting
Primary outcome(s)	Berg balance scale
Key secondary outcome(s)	Lower extremity of the Fugl–Meyer assessment; modified Barthel index; regional homogeneity, fractional amplitude of low frequency fluctuation and functional connectivity analyses from rs-fMRI.

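### The plan band-pass filters the data to 0.01–0.1 Hz before calculating fALFF, which removes the out-of-band signal that fALFF's own full-band denominator needs

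*Protocol article*

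**What the plan says.** All of the processing text is in the protocol article, Statistical Analysis, under Functional Magnetic Resonance Imaging Data Analysis.

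- **Order.** Preprocessing is a lettered list (a) to (g). It ends with the filter and the smoothing, and the three measures come next: "f) filter (0.01–0.1 Hz), and (g) smooth (8 mm full-width half-maximum Gaussian). Then, the ReHo, fALFF, and FC values will be calculated".
- **Numerator.** "The ALFF measurement is the root mean square of the power spectrum of the BOLD signal in the range of 0.01–0.1 Hz for each voxel".
- **Denominator.** "the ALFF value of each voxel divided by the full-band ALFF sum is the fALFF value".
- **Second mention of filtering.** In the FC description only: "In SPM12, after bandpass filtering and linear-trend removal, a reference time series for the seed will be extracted".
- **Test.** "Data will be analyzed by the independent-samples (between-group comparison) or paired (within-group comparison) *t*-test".

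The Secondary Outcomes section gives the functional acquisition as "TR = 2,000 ms, TE = 30 ms, FOV = 240 mm × 240 mm, slice thickness = 4 mm, FA = 90°, and 35 slices". Table 1 includes among the key secondary outcomes "regional homogeneity, fractional amplitude of low frequency fluctuation and functional connectivity analyses from rs-fMRI". No number of volumes, filter type or numerical limits for the full band are stated.

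**The concern.** fALFF is a ratio. It asks how much of a voxel's total signal amplitude lies in the low-frequency band, so it is informative only if amplitude outside that band is still in the data when the denominator is formed. The plan removes that amplitude first, with a filter whose pass-band is the numerator band.

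At stake is one of three imaging measures meant to support the neural-remodelling aim. If the written order is followed, neither a significant nor a null comparison between arms or between scans says what the plan intends about fALFF.

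**Working it through.** The plan gives no fALFF value to reproduce, so the check is of the order of operations, followed by a simulation of its size.

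**Inputs from the article.** Filter band 0.01–0.1 Hz; ALFF band 0.01–0.1 Hz; denominator over the full band; functional TR 2 s.

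**Assumed inputs.** 170, 230 or 470 retained volumes (not stated); AR(1) series with coefficient uniform on 0–0.8; 4,000 series per setting.

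**Step 1: what the filter removes.** Sampling rate = 1/2 s = 0.5 Hz, so the measurable band ends at 0.5/2 = 0.25 Hz. The filter takes out 0–0.01 Hz and 0.1–0.25 Hz, which is 0.01 + 0.15 = 0.16 Hz of 0.25 Hz, or 64% of the band. Smoothing combines neighbouring voxels linearly and cannot restore those frequencies.

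**Step 2: the ratio after an ideal filter.** Let A(f) be the amplitude at frequency f, B the 0.01–0.1 Hz band and F the full band.

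- Sum over sum: Σ_B A / Σ_F A. After filtering, A = 0 outside B, so the ratio is Σ_B A / Σ_B A = 1 for every voxel.
- Mean over sum: the ratio is 1/(number of in-band frequencies), again a constant: 1/31 = 0.0323, 1/42 = 0.0238 and 1/85 = 0.0118 for 170, 230 and 470 volumes.
- Root mean square over sum, the closest reading of the article's words: √(mean_B A²) / Σ_B A. This is not constant. It depends on how uneven the spectrum is inside B and on nothing outside B.

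**Step 3: size by simulation.** Coefficient of variation between series, for 170 / 230 / 470 volumes:

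| Processing | Sum over sum | RMS over sum |
|---|---|---|
| Unfiltered | 13.8 / 13.5 / 12.8% | 16.4 / 16.0 / 15.3% |
| Ideal filter first | 0 / 0 / 0% | 4.4 / 4.0 / 3.5% |
| Butterworth filter first | 4.7 / 4.2 / 3.3% | 7.5 / 6.9 / 6.0% |

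The mean sum-over-sum ratio is 0.46–0.47 unfiltered, 1.000 after the ideal filter and 0.84–0.86 after the Butterworth filter.

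**Step 4: what the remaining variation measures.** Unfiltered sum-over-sum fALFF correlates 0.88–0.95 with the AR coefficient, which sets the low-frequency content. RMS over sum after the ideal filter correlates 0.54–0.71 with it. Where the filtered version is not constant, it correlates between 0.616 and 0.872 with its unfiltered counterpart, so 38% (0.616²) to 76% (0.872²) of the variance is shared. This agreement is helped by the model: in an AR(1) series one parameter governs both the slope inside the band and the share outside it. Real BOLD spectra need not behave that way.

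**The case against.** The strongest case on the other side has three parts.

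**It is not a constant.** A reader might infer that fALFF becomes 1 in every voxel, cannot differ between arms, and can yield only artefacts. The document does not support that. It fixes the filter band but not the filter's shape, and it describes the numerator as a root mean square. Exact constancy needs an ideal filter together with a sum-over-sum or mean-over-sum definition. Otherwise the measure is degraded but retains some relation to low-frequency content, as step 4 shows. This part stands, and the conclusion is limited accordingly.

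**The list may be loose.** The steps are introduced as included rather than exhaustive, the FC paragraph mentions band-pass filtering again, and a full-band denominator presupposes that out-of-band signal is present. One could read this as filtering specified separately for each measure, with the detail left to a fuller document. The reading is possible but is not what the text says: the steps are lettered, the next sentence places all three measures after them, and nothing exempts fALFF. This is a stated order that conflicts with a stated definition, not an omitted detail. It does mean that nobody can infer from the article that the analysis actually run is faulty, because the software may be set to compute fALFF before filtering.

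**The reach is limited.** fALFF is one imaging measure among several secondary outcomes, and the order can be changed at any time before the imaging analysis. That is correct and bears on urgency. It does not make the written order right.

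**Conclusion.** The point holds as an internal conflict that gives a wrong result if followed. With the filter applied first, the quantity computed is not the low-frequency share of the full spectrum by which the article defines fALFF.

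Its size depends on choices the article leaves open: complete loss of variation under an ideal filter with matching sums, where a t-test has zero variance and is undefined; otherwise a between-series CV of 3.3–7.5%, against 12.8–16.4% unfiltered. These figures rest on the assumed volumes and on AR(1) series. They describe variation between simulated series, not between patients, so they do not convert directly into a loss of power. The algebra in steps 1 and 2 needs none of these assumptions beyond the ideal filter.

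The consequence is confined to fALFF. The Berg Balance Scale, the Fugl–Meyer lower-extremity score, the modified Barthel index, ReHo, FC and the sample size are untouched, so a reader should not infer that the efficacy conclusion or the whole imaging component fails.

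**What to change.** Split the pipeline after nuisance regression, and say so in the analysis section:

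- **ALFF and fALFF:** compute on detrended, nuisance-regressed, unfiltered data. Numerator 0.01–0.1 Hz; denominator the whole measurable band, up to 0.25 Hz at TR 2 s. State whether each is a sum, mean or root mean square of amplitude.
- **ReHo and FC:** apply the 0.01–0.1 Hz band-pass filter on these branches only.

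If the software is already set to compute fALFF before filtering, correct the text to match. The cost is a reordered script and a sentence or two in the plan. It needs no new data or scans and no change to patient procedures, and it should be settled before the imaging data are analysed.

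### The written fALFF formula divides an in-band average of power by a full-band sum, so it does not give the fractional amplitude named as a key secondary outcome, and its value changes with scan length

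*Protocol article*

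**What the plan says.** Table 1 of the protocol article lists among the key secondary outcomes "regional homogeneity, fractional amplitude of low frequency fluctuation and functional connectivity analyses from rs-fMRI". The Secondary Outcomes section uses the same name for fALFF.

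The section Functional Magnetic Resonance Imaging Data Analysis then gives the calculation:

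- Numerator: "The ALFF measurement is the root mean square of the power spectrum of the BOLD signal in the range of 0.01–0.1 Hz for each voxel".
- Ratio: "the ALFF value of each voxel divided by the full-band ALFF sum is the fALFF value".
- Trimming, preprocessing step (a): "removing the first 10–20 time points and slice timing".
- Order of the last steps: "f) filter (0.01–0.1 Hz), and (g) smooth (8 mm full-width half-maximum Gaussian). Then, the ReHo, fALFF, and FC values will be calculated".
- Software: SPM12 and the "data processing assistant for rs-fMRI software (DPARSF^2^) will be used for data processing and analysis".

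The functional run has "TR = 2,000 ms, TE = 30 ms, FOV = 240 mm × 240 mm, slice thickness = 4 mm, FA = 90°, and 35 slices". The article does not give the number of volumes acquired. Maps are compared by independent-samples t-test between groups and by paired t-test within groups.

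**The concern.** A fractional amplitude should be a part divided by its whole, both measured as amplitude (the square root of power). The written rule departs from this in two ways.

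1. The numerator is a mean-type quantity over the in-band bins, while the denominator is a sum over all bins. The result is not a share of anything, and it shrinks as the number of bins grows.
2. The root mean square is taken of the power spectrum. Read literally, that squares power and does not return an amplitude. The text also does not say whether the full-band sum is of power or of amplitude.

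A key secondary outcome therefore cannot be reproduced from its own definition, and published values could not be read as fractions. Because the trimming is given as a range, two scans with identical signal could also receive different values if they were trimmed differently.

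**Working it through.** The article states no fALFF value, so there is no figure to reproduce.

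**Inputs.** From the article: TR 2 s, band 0.01–0.1 Hz, 10 to 20 points discarded. Assumed: the number of volumes (120 to 1200 tried) and the shape of the spectrum.

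**Bins.** With N retained points at TR 2 s, the frequency spacing is 1/(2N) Hz and the highest frequency is 1/(2 × 2 s) = 0.25 Hz, so there are K = N/2 bins. For N = 240, the bins from 0.01 to 0.1 Hz are numbers 5 to 48, which is 44 of 120.

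**Is it a share?** Take the simplest case, a flat noise-free spectrum with power 1 in every bin.

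- Amplitude share: 44/120 = 0.367.
- Written rule: root mean square = 1 and full-band sum = 120, giving 1/120 = 0.0083. The result is the same whether the sum is of power or of amplitude.

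Simulated spectra at N = 240 (mixed spectrum, random periodogram) give:

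| Form | Mean value |
|---|---|
| In-band amplitude sum / full-band amplitude sum | 0.450 |
| Root mean square power / power sum | 0.0176 |
| Root mean square power / amplitude sum | 0.0209 |

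Under the last form the value also doubles when the signal is doubled (0.0209 to 0.0416), so it is not even scale-free.

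**Dependence on length.** Root mean square power / power sum is 0.0343 at 120 points, 0.0176 at 240, 0.0088 at 480 and 0.0036 at 1200. The true fraction stays at about 0.44–0.45 throughout.

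**Effect of the 10–20 range.** The written value scales as 1/K, so the shift from dropping 20 rather than 10 points is (V − 10)/(V − 20) − 1 for V acquired volumes:

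| V (assumed) | Bins, 10 dropped | Bins, 20 dropped | Shift |
|---|---|---|---|
| 120 | 55 | 50 | +10.0% |
| 180 | 85 | 80 | +6.25% |
| 240 | 115 | 110 | +4.5% |
| 300 | 145 | 140 | +3.6% |

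For comparison, the flat-spectrum amplitude share at V = 240 goes from 42/115 = 0.3652 to 40/110 = 0.3636, a change of −0.4%.

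**Equal length.** If every scan has the same K, the factor 1/K multiplies every value alike. It cancels from mean difference over standard error, so the t statistics do not change.

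**Interaction with the filter.** The 0.01–0.1 Hz filter is listed before fALFF is calculated. If it removes everything outside the band, the in-band and full-band sums are the same sum, and the amplitude fraction is 1.000 in every scan. Under the power-sum reading of the written rule, a 20% rise in in-band amplitude multiplies numerator and denominator alike by 1.2² = 1.44 and cancels. The simulated standardised effect is accordingly about 0. Correcting the ratio alone would therefore turn the outcome into a constant.

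**The case against.** The strongest reply is that the two sentences only explain the metric in a condensed article, and that the named software will do the calculation. That is possible, and the documents do not settle it. But if the software computes a proper fraction, the published sentence still misdescribes the outcome. This is a stated rule that is wrong, not a detail left out.

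A second reply is that nothing shows scan length will vary. There is one acquisition protocol, the quality-assurance section calls for unified indices and standard operating procedures, and statisticians are blinded. This largely stands. A reader might infer from the 10–20 range that the treatment comparison will be biased. The documents do not support that, because nothing ties the number of discarded points to arm or visit, and at equal length the t-tests are untouched.

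A reader might also infer that the written rule makes the outcome noisier and costs power with 20 patients per arm. The documents do not support that either:

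- It depends on the reading. If the numerator is taken loosely as mean amplitude, the coefficient of variation and the standardised effect are exactly those of the true fraction.
- It depends on the spectrum. With a flat spectrum, root mean square power over amplitude sum is not worse for a 20% in-band rise (standardised effect 1.93 against 1.82, single voxel).
- It nearly vanishes with patient variation. With an assumed between-patient log-SD of 0.2, 20 independent voxels averaged and a mixed spectrum, the two literal forms give standardised effects of 0.93 and 0.91 against 0.94, and power of 0.838 and 0.817 against 0.842.

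**Conclusion.** The point holds as an error of definition. The formula as written is not the fractional amplitude named as a key secondary outcome. It gives values of about 0.02 where the fraction is about 0.45 (240 points, mixed spectrum assumed), and it scales with about 1/(number of bins).

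The practical risk is conditional. Unequal trimming within the stated 10–20 range would shift values by about 4.5% at an assumed 240 acquired volumes (3.6% at 300, 10% at 120) with no change in signal. With equal trimming there is no effect on the tests. No loss of precision or power is established.

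Severity is low. One imaging secondary outcome is affected; the Berg Balance Scale analysis and the sample size are not. The volume counts and spectra are assumptions, because the article gives neither.

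**What to change.** Replace the two defining sentences with wording such as: fALFF is the sum of spectral amplitude (square root of power) over 0.01–0.1 Hz divided by the sum of spectral amplitude over the full measurable band (up to 0.25 Hz at TR 2 s), computed on data before the band-pass filter in step (f). The last clause is essential, because after that filter the ratio is 1 in every scan.

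Replace the 10–20 range with one number applied to every scan of every patient, and confirm that the DPARSF settings produce the defined quantity.

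The cost is a few words, one fixed preprocessing number and a check of settings. No new patients, scans or procedures are needed. If the larger discard number is chosen, a few more volumes per scan are lost.
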